### Visual Analogue Scale (VAS) for maximum pain level

2.9

Patients will be questioned about the severity of their maximum pain level during RT procedures and will have to mark the pain level on a 10-cm line, where 0 represents “not painful at all” and 10 “extremely painful.”

### Skindex-29

2.10

Skindex-29 is a patient-rated questionnaire to measure QoL of patients with skin diseases every 4 weeks, consisting of 30 items.^[23]^ It is a 5-level Likert scale from 1 (never) to 5 (always). The Korean version of Skindex-29 has been validated.^[24]^

### Safety assessment

2.11

The adverse events will be evaluated and reported during the study. Local rash, rubescent, or itching are expected to be found from time to time. If an adverse reaction is found, then the investigators will assess the intensity/frequency of each episode and decide whether further treatments are necessary or not. Vital signs will be regularly checked to assess JUG safety.

### Pharmacoeconomic evaluation

2.12

EuroQoL Five Dimensions questionnaire (EQ-5D) will be used to assess the pharmacoeconomic evaluation of JUG in breast cancer patients. The EQ-5D comprises 5-level questions on mobility, self-care, usual activities, pain/discomfort and anxiety/depression, and VAS. Quality adjusted life year (QALY) will be calculated with the EQ-5D results, which will be combined with medical cost survey to estimate the incremental cost-utility ratio and incremental cost-effectiveness ratio. We will use the validated Korean version of this outcome.^[25]^

The iMTA Productivity Cost Questionnaire (iPCQ) will assess the health-related productivity losses. This questionnaire has 12 items and the patients have to answer each by recalling the previous 4 weeks.^[26]^

### Sample size

2.13

In the pilot study, occurrence rate of RD with RTOG toxicity grade 2 or more was 46.7% and 78.6% in the JUG and GSC groups, respectively.^[20]^ The null hypothesis is that *S*_*JUG*_ (t) = *S*_*GSC*_ (t), where *S* denotes the probability that RD does not occur during RT of breast cancer patients (*S*_*JUG*_ (t) = 53.3%, *S*_*GSC*_ = 21.4%). The sample size has been calculated as 36 per group (two-sided, α = 0.05 and 1-β = 0.8) with logrank test of PASS software version 14.0.11 (NCSS Statistical Software). With a 10% drop-out rate expected, we have decided to enroll 80 eligible participants (40 in each group).

### Statistical analysis

2.14

The primary outcome is the incidence rate of RD graded 2 or more on the RTOG toxicity scale. These results will be statistically compared between groups using the logrank test after estimating the survival curve with Kaplan–Meier method. Any continuous variables will be tested independently with *t* test or Mann–Whitney *U* test according to the normality of the distribution. The adverse events will be tested with Chi-square or Fisher exact test. Paired *t*test or McNemar test will be adopted to compare the vital signs results within a group. All the data will be analyzed at a significance level of .05 (two-sided) with R software version 3.5.2 or later.

The primary analysis will include all the participants assessed with the RTOG toxicity scale at least once after randomization (full analysis set). Secondarily, per protocol set will be analyzed, which is defined as the group of participants complying with the trial procedure, including the study drug use, at least 80%. Safety set is defined as the participants who use the study drug at least once.

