### Study design and setting

2.2

This is a prospective, open-label, parallel-group, randomized controlled trial. This study will enroll 80 female patients, who have been diagnosed with unilateral breast cancer confirmed by biopsy and supposed to undergo RT of 50 to 64 Gy dose after breast conserving surgery. They will be allocated to either the JUG or GSC group with an allocation ratio of 1:1. Both groups will be subjected to GSC, but only the JUG group will apply the adjuvant JUG ointment on the irradiated skin for 6 weeks, twice a day. Eligible participants will be enrolled from the in-patients or out-patients of the Kyung Hee University Korean Medicine Hospital, Seoul, Republic of Korea. Study advertisements will be posted on webpages and notice boards to promote subject enrollments.

The study flow is depicted in Figure 1.

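### The normality-based rule sends skewed costs to Mann-Whitney, while the incremental cost ratios rest on differences in mean cost, so the reported p-value can disagree with the ICER numerator, even in sign

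*Protocol article*

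**What the plan says.** Section 2.14 (Statistical analysis) sets one rule: "Any continuous variables will be tested independently with *t* test or Mann–Whitney *U* test according to the normality of the distribution". It makes no exception for economic variables and adds "All the data will be analyzed at a significance level of .05 (two-sided) with R software version 3.5.2 or later".

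Section 2.12 (Pharmacoeconomic evaluation) derives QALYs from the EQ-5D, "which will be combined with medical cost survey to estimate the incremental cost-utility ratio and incremental cost-effectiveness ratio". It adds a second cost-type variable: "The iMTA Productivity Cost Questionnaire (iPCQ) will assess the health-related productivity losses". The section gives no separate method for comparing costs between arms. Economic evaluation is part of the title and of the aims in the Introduction and section 2.1, though it is not the primary objective.

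**The concern.** An incremental cost ratio is a between-arm difference in mean cost divided by a difference in mean effect. Mean cost is what a payer can multiply by the number of patients. Mann-Whitney asks a different question: whether a cost drawn from one arm tends to exceed a cost drawn from the other. The two questions coincide when the arms' distributions have the same shape and separate when they do not.

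A difference in shape is plausible here. Under section 2.5 every JUG participant receives the same ointment supply, which adds a similar amount to every cost in that arm. Any saving would come from fewer patients with dermatitis costs, some of them possibly large. Ranks count the uniform addition in full and discount the large costs. Costs are usually skewed, and skewed data are what the rule sends to Mann-Whitney. The paper could then report JUG as significantly costlier beside an ICER whose numerator is near zero or negative.

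**Working it through.** **Patients per arm.** Section 2.13 gives the pilot rates ("occurrence rate of RD with RTOG toxicity grade 2 or more was 46.7% and 78.6% in the JUG and GSC groups, respectively") and the result ("The sample size has been calculated as 36 per group (two-sided, α = 0.05 and 1-β = 0.8) with logrank test").
- Hazard ratio = ln(0.533)/ln(0.214) = 0.408.
- Freedman events = (1.960 + 0.842)² × [(1 + 0.408)/(1 − 0.408)]² = 44.4, rounded up to 45.
- Mean event probability = (0.467 + 0.786)/2 = 0.6265, so N = 45/0.6265 = 71.8, or 36 per group; 36/0.9 = 40 enrolled per group.

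The stated sample size reproduces, so 36 and 40 per arm are used below.

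**Cost model (assumed, except for the dermatitis rates).**
- Dermatitis cost, when it occurs: lognormal, mean 1, log-SD *s*.
- GSC cost = other cost + Bernoulli(0.786) × dermatitis cost.
- JUG cost = other cost + Bernoulli(0.467) × dermatitis cost + ointment cost.
- Ointment cost is set at 0.786 − 0.467 = 0.319, which makes the true means equal.

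**Why ranks and means separate.** Take no other cost and *s* = 1.5. The median dermatitis cost is exp(−1.5²/2) = 0.325, and the chance that a dermatitis cost is below 0.319 is Φ[(ln 0.319 + 1.125)/1.5] = 0.495. A JUG patient costs more than a GSC patient in three cases:
- always, if the GSC patient has no dermatitis (0.214);
- with probability 0.495, if only the GSC patient has it;
- with probability above 0.5, if both have it, because JUG carries the extra 0.319.

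So P(JUG > GSC) is at least 0.214 + 0.786 × (0.533 × 0.495 + 0.467 × 0.5) = 0.605, although the means are equal.

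**Rejection by two-sided Mann-Whitney at 0.05, equal true means** (4,000 simulated trials per cell):

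| Other cost | n per arm | *s* = 0.8 | *s* = 1.2 | *s* = 1.5 |
|---|---|---|---|---|
| none | 36 | 8% | 40% | 75% |
| mean 1, CV 10% | 36 | 6% | 33% | 67% |
| mean 1, CV 30% | 36 | 5% | 13% | 28% |
| mean 1, CV 100% | 36 | 5% | 8% | 11% |
| none | 40 | 8% | 44% | 79% |

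The Welch t test rejects in 3.5% to 5.3% throughout. Where the rate is clearly inflated, nearly all rejections name JUG as costlier. The article names no normality test; Shapiro-Wilk at 0.05 in either arm would send at least 98.6% of these data sets to Mann-Whitney.

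**When a common cost dominates** (same model, 36 per arm, 2,000 trials per cell):

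| Other cost | *s* = 1.2 | *s* = 1.5 |
|---|---|---|
| mean 3, CV 30% | 6.2% | 7.2% |
| mean 5, CV 30% | 5.2% | 5.6% |
| mean 10, CV 10% | 4.8% | 6.0% |

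**Sign conflict.** With 36 per arm, no other cost and *s* = 1.5, Mann-Whitney calls JUG significantly costlier in 27% of trials while the observed JUG mean is the lower one.

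**A second set of scales** (40 per arm; other cost mean 100, log-SD 0.5 to 1.0; ointment cost 10 or 30; dermatitis cost mean 10/0.319 = 31 or 30/0.319 = 94, log-SD 1.0 or 1.5). At the pilot rates with equal means, Mann-Whitney declares JUG costlier in 2.5% to 15% of trials, against a nominal 2.5% in that direction. Welch rejects in 4% to 5%, two-sided.

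**The case against.** Section 2.12 plans estimates and names no test on cost. The rule in 2.14 may have been written with clinical outcomes in mind, and a health-economic plan that is not shown may replace it. This stands as a limit. The wording still has no exception, and if another plan differs, the sentence in 2.14 conflicts with it.

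The size is also open to challenge. The article gives no unit costs, skewness or share of zero costs, and does not say whether the survey counts radiotherapy. If it does, a common cost several times the dermatitis cost is plausible and the inflation nearly vanishes. Section 2.6 also bars other management of dermatitis during the study, which limits large dermatitis costs, although section 2.11 leaves room for treating adverse reactions. All of this stands.

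A reader might infer several stronger claims, which the article does not support:
- *The ICER itself is wrong.* The choice of test does not change the point estimate.
- *The error rate at least doubles whenever skew is strong.* The common-cost table shows rates near nominal at log-SD 1.2 and 1.5 with only modest variability in the other costs.
- *The same distortion has been shown for QALYs and productivity losses.* Only costs were simulated; the argument about means carries over to the others by reasoning alone.
- *The absence of a cost-effectiveness plane or acceptability curve is a fault.* An article may leave that detail to the full plan.

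**Conclusion.** The point holds as a mismatch between a stated rule and the quantity it would serve. For skewed costs, section 2.14 as written tests stochastic ordering, while section 2.12 needs a difference in means.

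The mismatch does not depend on the cost distribution, but its consequence does. Across the assumptions shown, the false-positive rate at equal mean cost with 36 per arm runs from about 5% to about 75%. The high end requires that dermatitis cost be most of the total and strongly skewed. Which end applies cannot be settled from the article. Since this is an additional aim and the ratios themselves are untouched, the change is worthwhile but does not bear on the primary result.

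**What to change.** In section 2.14, exempt costs from the normality-based rule and, for the same reason, productivity losses and QALYs. Suggested wording: *Costs, productivity losses and QALYs will be compared as differences in arithmetic means (JUG minus GSC) with a bootstrap 95% confidence interval, resampling patients within arm. Cost and QALY will be resampled jointly to express the uncertainty of the incremental ratios. The Mann-Whitney test will not be used for these variables.* A Welch interval is an acceptable alternative for the mean differences.

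This costs one or two sentences and a short R program. It needs no new data and leaves the sample size unchanged. The downside is wider intervals when costs are heavily skewed. Methods for means are not perfect at this size either: with lognormal costs of very different shape in the two arms (log-SD 0.5 against 1.2, 40 per arm, equal means) Welch rejected in about 11% of trials, but Mann-Whitney rejected in 78%.

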### Objectives and hypothesis

2.1

The primary objective of this study is to evaluate the effectiveness of adjuvant application of JUG on the irradiated skin of breast cancer patients undergoing RT after breast conserving surgery, with comparison of only GSC treatment. This will be assessed by the incidence rate of RD with RTOG toxicity grade of 2 or more. The secondary outcomes to be assessed and compared between the JUG and GSC arms include the time of initial RD occurrence, RD duration, maximum pain level, and quality of life (QoL). Additionally, the safety and pharmacoeconomic variables will be evaluated for JUG application in breast cancer patients.

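### The t test or Mann-Whitney rule for every continuous variable is valid, but it forgoes baseline adjustment for Skindex-29, EQ-5D and QALYs, which costs precision and leaves chance baseline differences in place

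*Protocol article*

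**What the plan says.** Section 2.14 of the protocol article sets the rule for continuous outcomes: "Any continuous variables will be tested independently with *t* test or Mann–Whitney *U* test according to the normality of the distribution". The section names no covariate, change score or longitudinal model for comparing the arms. Its only paired tests are within group and concern vital signs.

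The outcomes that the rule reaches are these:

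- Section 2.1 lists the between-arm secondary outcomes as "time of initial RD occurrence, RD duration, maximum pain level, and quality of life (QoL").
- Section 2.10 describes Skindex-29 as an instrument to "measure QoL of patients with skin diseases every 4 weeks".
- Section 2.12 states that "Quality adjusted life year (QALY) will be calculated with the EQ-5D results", and combines the QALYs with cost data to estimate incremental cost-utility and cost-effectiveness ratios.

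Section 2.4 describes 1:1 allocation and states no stratification by baseline quality of life or utility. Section 2.13 plans 36 evaluable and 40 enrolled patients per arm.

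**The concern.** Patients will start radiotherapy with differing quality of life and utility. A two-sample test on follow-up values leaves all of that variation in the error term. Where the patient's own starting score is available and predicts the later one, a model that includes it estimates the same treatment difference with a smaller standard error. It also removes the part of the observed difference that is due to the arms having started apart.

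For QALYs the point concerns the estimate as well as the test. In an area-under-the-curve QALY the starting utility is one component of the outcome, so a difference present before any ointment is applied becomes part of the incremental QALY. That quantity is the denominator of the cost-utility ratio. Over a 42-day course it is bound to be small, so modest shifts matter.

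**Working it through.** **Inputs from the document.** Two-sided α = 0.05 and power 0.80, event-free proportions 53.3% and 21.4%, 36 per group, 10% drop-out and 40 per group enrolled (all section 2.13); a 42-day course (section 2.5).

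**Assumed inputs, because the document gives none.** Baseline/follow-up correlation ρ from 0.2 to 0.7; utility SD 0.10 to 0.20; utilities taken at 0 and 6 weeks, or at three equally spaced times.

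**1. The plan's own figure.** HR = ln(0.533)/ln(0.214) = 0.408. Freedman's formula gives 45 events. N = 2 × 45/(2 − 0.533 − 0.214) = 71.8, so 36 per group, and 36/0.9 = 40. The sample size reproduces, and nothing below changes it.

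**2. Precision.** ANCOVA multiplies the residual SD by √(1 − ρ²). With 36 per group the unadjusted detectable difference at 80% power is (1.960 + 0.842) × √(2/36) = 0.66 SD (normal approximation). Power after adjustment at that same effect is Φ(2.802/√(1 − ρ²) − 1.960).

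| Assumed ρ | √(1 − ρ²) | Power after adjustment (unadjusted 80%) | Detectable difference, SD | n per group for 0.66 SD |
|---|---|---|---|---|
| 0.2 | 0.980 | 81.6% | 0.65 | 35 |
| 0.3 | 0.954 | 83.6% | 0.63 | 33 |
| 0.5 | 0.866 | 89.9% | 0.57 | 27 |
| 0.7 | 0.714 | 97.5% | 0.47 | 19 |

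The last column is 36 × (1 − ρ²), rounded up. A noncentral-t calculation gives the same powers with 36 or 40 per arm to within 0.001; its starting effects are 0.670 SD and 0.634 SD respectively. At a fixed effect of 0.5 SD with 36 per group, power is 56% unadjusted and 60%, 69% and 84% adjusted at ρ = 0.3, 0.5 and 0.7.

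**3. Chance imbalance.** The standard error of the baseline mean difference is √(2/36) = 0.236 SD, or √(2/40) = 0.224 SD. With 40 per arm, P(|imbalance| > 0.25 SD) = 2 × [1 − Φ(0.25/0.224)] = 26%. In 40,000 simulated null trials with 36 per arm, the unadjusted t test rejected in about 5% overall. Among trials with a baseline imbalance near 2 SE it rejected in about 14% (ρ = 0.5) or 20% (ρ = 0.7). Among those near 1 SE it rejected in 4.8% or 3.7%.

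**4. QALY, if computed as area under the curve.** With utilities at 0 and 6 weeks joined by a straight line, mean utility is (U₀ + U₆)/2. Its slope on baseline utility is (1 + ρ)/2 = 0.65, 0.75 and 0.85 at ρ = 0.3, 0.5 and 0.7. With three equally spaced assessments and equal correlations, the slope is 0.25 + 0.75ρ = 0.48, 0.63 and 0.78. With two assessments, ρ = 0.5 and 36 per arm, a 1-SE imbalance shifts the QALY difference by SD × 0.236 × 0.75 × 6/52. That is 0.002 QALY at SD 0.10 and 0.004 at SD 0.20.

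**The case against.** **The test is valid.** A reader might infer that the unadjusted comparison is biased or inflates false positives. It does neither: under randomisation the two-sample test is unbiased and its overall type I error is about 5%, as the simulation shows. The rates of 14% and 20% apply only to trials with an unusually large imbalance. A reader might also say that the test ignores the pairing of values within a patient. That does not apply to a comparison at one visit, or to a QALY, which is one value per patient.

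**The text names a test, not the variable tested.** Change scores are not excluded, and they would remove the starting difference from Skindex-29. This stands as a limit. Change scores multiply the SD by √(2(1 − ρ)), however, so with 36 per group the detectable difference is 0.78, 0.66 and 0.51 SD at ρ = 0.3, 0.5 and 0.7. ANCOVA gives 0.63, 0.57 and 0.47. Change scores also do not correct an area-under-the-curve QALY.

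**An article may leave covariates to the full protocol or analysis plan.** That would answer a complaint about silence. Section 2.14 is not silent, though: its rule covers all continuous variables.

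**The QALY method is not stated.** Section 2.12 does not say how QALYs are computed, and section 2.14 does not mention them by name. The QALY part is therefore conditional. The documents do not support a claim that the plan's incremental QALY will carry the imbalance, only that it will do so if the usual area-under-the-curve method is used without adjustment.

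**The schedule is not visible.** Figure 1 is not shown, and the four-week phrase in section 2.10 could describe the instrument rather than the visits. The existence of a pre-radiotherapy questionnaire is inferred, chiefly because a QALY ordinarily needs a starting utility.

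**The correlation may be low.** Radiation dermatitis has not yet occurred at entry, and section 2.3 excludes damaged breast skin. Baseline Skindex-29 scores may be compressed and predict little. This is fair, and at ρ = 0.2 the gain is 1.6 points.

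**Conclusion.** This is an efficiency improvement for secondary and economic outcomes, not the correction of an error. The stated rule gives a valid test that is less precise than a baseline-adjusted one whenever the starting score predicts the later one. It also leaves chance baseline differences in the comparison.

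The gain is from 80% to about 84%, 90% or 97% power at ρ = 0.3, 0.5 or 0.7, and it passes 5 points only from about ρ = 0.4 (86.4%). For an area-under-the-curve QALY, a 1-SE imbalance moves the incremental QALY by about 0.002 to 0.004. All these sizes rest on assumed correlations, SDs and assessment times. The effect used as the benchmark is the one that gives 80% power unadjusted; the trial plans no particular quality-of-life effect. The primary logrank analysis and the sample size are untouched.

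**What to change.** Amend section 2.14, provided the pre-radiotherapy questionnaires are collected (to be confirmed against Figure 1):

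- **Skindex-29, EQ-5D index and EQ-5D VAS:** compare arms by ANCOVA of the follow-up score on arm plus the patient's own baseline score, or by a mixed model over visits with baseline as covariate.
- **QALY:** estimate the between-arm difference by regression on arm plus baseline EQ-5D utility, and use that adjusted difference in the cost-utility ratio.
- **Supportive analysis:** keep the t test or Mann-Whitney test.

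The cost is wording and one degree of freedom per model. It needs no added patients or visits, and no new data if the baseline forms already exist. Because the trial is open-label, fixing the covariate before the data are seen also prevents its being chosen afterwards.

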There have also been a few clinical trials that explored the effectiveness and safety of JUG in RD. Patients undergoing RT for brain tumors showed favorable improvement or meaningful prevention of scalp dermatitis after topical application of JUG.^[18,19]^ A pilot study randomly allocated 30 breast cancer patients and evaluated the incidence of RD with Radiation Therapy Oncology Group (RTOG) toxicity of grade 2 or more, resulting in lowering of the RD incidence in the JUG treatment group with no safety issues, as compared to the general supportive care (GSC) group.^[20]^

This study protocol is primarily aimed at showing the effectiveness and safety of the adjuvant application of JUG for RD in breast cancer patients undergoing RT, as compared to GSC, along with its pharmacoeconomic evaluation.

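### The Introduction aims to show that JUG is safe, but the only between-group adverse-event analysis stated is a 0.05 difference test, which cannot support that conclusion

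*Protocol article*

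**What the plan says.** The last paragraph of the Introduction gives the purpose as "This study protocol is primarily aimed at showing the effectiveness and safety of the adjuvant application of JUG". Section 2.1 (Objectives and hypothesis) is more modest. Its primary objective is effectiveness only, and safety follows as an addition: "Additionally, the safety and pharmacoeconomic variables will be evaluated for JUG application in breast cancer patients". The Abstract and the Discussion likewise speak of evaluating safety.

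For the analysis, section 2.14 states "The adverse events will be tested with Chi-square or Fisher exact test" and adds "All the data will be analyzed at a significance level of .05 (two-sided) with R software version 3.5.2 or later". The other safety analysis named there is within-arm: a paired t test or "McNemar test will be adopted to compare the vital signs results within a group". Section 2.11 describes episode-by-episode assessment of intensity and frequency and regular vital-sign checks. It names local skin reactions as expected but gives no rates.

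Section 2.13 derives 36 per group from a logrank test on grade 2 or higher dermatitis and then, for 10% dropout, "we have decided to enroll 80 eligible participants (40 in each group"). No safety quantity enters that calculation.

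**The concern.** A Chi-square or Fisher test addresses the hypothesis that the two arms have the same adverse-event rate. Rejecting it in the unfavourable direction is evidence of harm. Not rejecting it is compatible with no excess, and equally with an excess too small for the trial to detect. The test therefore cannot deliver what the Introduction sets out to show.

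If few patients have events, non-significance is the expected outcome whether or not JUG causes a moderate excess of local reactions. Any safety statement resting on that p-value would carry little information, and nothing in the stated output would tell readers how large an excess remains possible. A risk difference with its interval would tell them.

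**Working it through.** **1. The plan's own sample size, and what it covers.** Inputs from section 2.13: dermatitis-free probabilities 0.533 (JUG) and 0.214 (GSC), two-sided 0.05, 80% power.
- Hazard ratio = ln(0.533)/ln(0.214) = 0.408.
- Freedman events = (1.960 + 0.842)² × [(1 + 0.408)/(1 − 0.408)]² = 44.4, rounded up to 45.
- Patients per group = 45/(2 − 0.533 − 0.214) = 45/1.253 = 35.9, so 36. With 10% dropout, 36/0.9 = 40.

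Both stated figures are reproduced, from efficacy inputs alone.

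**2. How often the stated tests miss an excess.** For true rates p₀ (GSC) and p₁ (JUG) and n per arm, the power is the sum over all count pairs (a, b) of Bin(a; n, p₁) × Bin(b; n, p₀), taken where the two-sided p is at most 0.05. The miss rate is 1 minus the power. All rates below are assumptions. Chi-square is without continuity correction.

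| GSC vs JUG | Excess (points) | Fisher miss, n = 40 | Chi-square miss, n = 40 | Fisher / Chi-square miss, n = 36 |
|---|---|---|---|---|
| 5% vs 15% | 10 | 82% | 65% | 85% / 68% |
| 10% vs 20% | 10 | 84% | 75% | 86% / 78% |
| 5% vs 20% | 15 | 59% | 43% | 66% / 47% |
| 10% vs 25% | 15 | 67% | 56% | 71% / 61% |
| 5% vs 30% | 25 | 18% | 11% | 24% / 15% |
| 10% vs 40% | 30 | 15% | 10% | 20% / 14% |

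At 40 per group, 10-point excesses are missed in 65% to 84% of trials and 15-point excesses in 43% to 67%. Excesses of 25 to 30 points are usually detected.

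**3. What a single result would look like.** With no GSC events among 40, Fisher is not significant at 5 JUG events (p = 0.055) and becomes so at 6 (p = 0.026).

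Take 7/40 on JUG and 2/40 on GSC, a difference of 0.175 − 0.050 = 0.125, with Fisher p = 0.15. The Wilson limits are 0.087 to 0.319 (JUG) and 0.014 to 0.165 (GSC). The Newcombe interval is then:
- lower = 0.125 − √[(0.175 − 0.087)² + (0.165 − 0.050)²] = −0.020
- upper = 0.125 + √[(0.319 − 0.175)² + (0.050 − 0.014)²] = 0.274

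The p-value alone would be reported as no significant difference. The interval shows that an excess of up to 27 points is not excluded.

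**4. The best case.** With 0/40 events on JUG, the two-sided 95% Clopper-Pearson upper limit is 1 − 0.025^(1/40) = 8.8%. Even equal low counts leave room: 2/40 in each arm gives a difference of 0 with a Newcombe interval of −12.1 to +12.1 points.

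**The case against.** The strongest reply is that the plan never says a non-significant p will be read as safety. That is correct. A reader might infer such a rule from the Introduction and section 2.14 together, but no text states it. What stands is narrower: the stated aim and the stated test do not match.

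Second, only the Introduction speaks of showing safety; the Abstract, section 2.1 and the Discussion speak of evaluating it. This also stands, and it limits the point. The remedy for the Introduction is to bring it into line with the rest of the article.

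Third, safety does not rest on one p-value, because section 2.11 describes clinical review of each episode and section 2.7 independent monitoring. These are useful, but they do not compare the arms.

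Fourth, a journal article condenses a fuller protocol, and intervals may be set there or in the analysis plan. Their absence here is therefore not itself the fault. The point concerns a method that the article does name for an aim that it does state.

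Fifth, a reader might go further and say that relevant harms would usually be missed, or that even a doubling or quadrupling of the rate would go undetected. The documents do not support this. They give no adverse-event rate and no threshold for relevant harm, and the claim fails for many inputs: 10% versus 40% is missed in only 15% (Fisher) or 10% (Chi-square) of trials, and Chi-square detects 5% versus 20% more often than not.

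Finally, a formal safety margin is not a required part of a trial sized for efficacy, and none is asked for.

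**Conclusion.** The concern holds as a mismatch between aim and method. The Introduction sets out to show safety, and the only between-group adverse-event analysis stated is a two-sided 0.05 difference test in a trial sized for another endpoint. That test can signal a large excess, but its non-significance cannot support a conclusion of safety. For excesses of 10 points over a 5% to 10% base, non-significance is the likelier result under either test. At 15 points, the likelier result depends on the test and the base rate.

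These sizes rest on assumed rates, full follow-up of 40 per group and an uncorrected Chi-square; 36 per group gives somewhat higher miss rates. The primary analysis, the sample size and the efficacy conclusion are unaffected. This is a cheap improvement worth making, not a flaw that threatens the trial.

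**What to change.** In section 2.14, make estimation the basis of the safety statement. Suggested text: *Adverse-event incidence will be reported per arm, and the JUG minus GSC risk difference will be given with a 95% (Newcombe) confidence interval. The safety statement will be based on this estimate and interval. The Chi-square or Fisher p-value is supportive, and a non-significant result will not be interpreted as evidence of safety.*

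The risk difference needs a GSC denominator. Section 2.14 defines the safety set by use of the study drug, which only the JUG arm receives, so the text should also name the GSC participants who enter this comparison.

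In the Introduction, replace the aim of showing safety with evaluating or describing it, as in the Abstract, section 2.1 and the Discussion.

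The cost is wording only: no added patients, data or safety margin. The downside is a less favourable-sounding safety statement, since even no events among 40 JUG patients would exclude only rates above about 9%.
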